## Data before extubation:

- Delta POCC \_\_\_\_\_(cmH20)
- Muscle \_\_\_\_\_pressure (cmH20)
- P0.1 (Pressure in 0.1 seconds) \_\_\_\_\_(cmH20)
- Amount of secretions by tube orotracheal \_\_\_\_\_(Yes/No)
- Index of asynchronies \_\_\_\_(% )
- NIF \_\_\_\_\_(cmH20)
- Percentage of drain \_\_\_\_(% drain)
- Beak flow cough \_\_\_\_ (L/min)

- Measurement of excursion diaphragmatic (cm)
- Measurement of percentage of thickness diaphragmatic (cm)
- OMAHA to the Moment of Extubation: \_\_\_\_\_ (+/- )

### Later to extubation:

- Dysphonia at 72 Hours: \_\_\_\_\_ (Yes/No)
- Maximum Mobility Extent by JH-HLM at 24 hours: \_\_\_\_\_
- Force Prehensile at 24 hours: \_\_\_\_\_
- Need of Ventilation Mechanics No Invasive to the 48 hours: \_\_\_\_\_ (Yes/No)
- Dysphagia to the 72 Hours: \_\_\_\_\_ (Yes/No)
- Start of Track Oral: \_\_\_\_\_ (1: 12-24 hours, 2> 24 hours).
- Failure Extubation at 48 hours: \_\_\_\_\_ (Yes/No)
- Force Muscular Measured with the scale MRC to the 24 hours: \_\_\_\_\_

### Final observational:

#### Functionality and Stay:

- Index by Barthel to the Egress hospitable: \_\_\_\_\_
- Function cognitive measured by MOCHA: \_\_\_\_\_
- Test fast of sensitivity and skill: \_\_\_\_\_
- Days of Hospital Stay: \_\_\_\_\_ (the day when the intensivist informs transfer to the floor).
- Time of Stay in ICU: \_\_\_\_\_ (days).
- Mortality: \_\_\_\_\_ (yes/no)
- State of Independence Functional Measured by ADLs to the Egress Hospitable: \_\_\_\_\_
- State of Independence Functional Measured by ADLs to the Egress of the ICU: \_\_\_\_\_

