**Multidisciplinary Coordination:** Promoting collaboration among healthcare professionals, including doctors, nurses, therapists, and other specialists, to ensure comprehensive and personalized care.

**Communication with Family Members:** Maintaining clear and regular communication with the patient's family, providing information about the patient's condition, and offering emotional support.

**Crisis Management:** Being prepared to address emergencies and make quick and effective decisions in response to acute changes in the patient's condition.

Interventions will be performed daily once the patient has been included in the study and will be carried out according to the expert consensus recommending mobilization maneuvers when the patient has an FIO2 less than or equal to 0.6, a percutaneous oxygen saturation greater than or equal to 90%, a respiratory rate less than 30 breaths per minute, and a PEEP less than or equal to 10 cmH2O.

These maneuvers will be performed until the patient is discharged (defined as the moment when the intensivist determines that the patient can be transferred to hospitalization or discharged from the hospital) from the ICU.

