## 6.6. Outcomes

### *Effectiveness*

Main outcome: time (days) from intubation to extubating.

- Secondary outcomes:

- Days free of mechanical ventilation until day 28
- Days of delirium until day 28
- Time in ICU with delirium until day 28
- Days of hospitalization with delirium until day 28
- Days of sedation until day 28
- Sedation-free days until day 28
- Extubating failure
- Need for non-invasive mechanical ventilation
- Exploratory outcomes:
- Barthel index at discharge
- Days of hospital stay
- Length of stay in ICU
- Mortality from any cause up to 90 days
- Time from intubation to start of therapy
- Muscular strength measured with the Medical Research Council (MRC) scale
- Dysphagia 72 hours after extubation
- Dysphonia 72 hours after extubation
- Time until initiation of oral administration post-extubation
- Development of healthcare-associated pneumonia,
- Maximum mobility measured by JH-HLM
- Grip strength
- Cognitive function measured using the Montreal Cognitive Assessment (MOCA)
- Evaluation of functionality in daily activities until day 28
- Quick sensitivity and dexterity test

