## 6.7. Measurements

Within the framework of the protocol, measurements will be conducted at six key moments of the research: upon admission to the intensive care unit, during observation in the intensive care unit, at the start of ventilatory support weaning, post-extubation, upon hospital discharge, and at the end of the observation period. Additionally, continuous measurements of outcomes associated with the safety of the intervention will be performed.

Upon admission, crucial details about each patient will be collected, such as name, identifier code, medical record number, sex, and ethnicity. Health and functionality aspects will also be evaluated, including the Barthel Index and Body Mass Index. Diagnostic information will be complemented with the ICD-10 code, study group (early vs. late), and the unit of admission (surgical, neurological, septic and respiratory, cardiovascular, or burn unit). Severity scores such as SOFA, APACHE II, and SAPS II will be incorporated, along with temporal data such as admission date, discharge date, and the time elapsed from intubation to the start of therapy. Regarding respiratory parameters, fundamental variables at the time of intubation will be detailed, such as tidal volume, respiratory rate, PEEP, plateau pressure, static lung compliance, driving pressure, airway resistance, and the PaO2/FIO2 ratio.

During the observation phase, a rigorous daily patient evaluation process will be implemented to ensure accurate recording of their progress. Key variables will be monitored, such as days on mechanical ventilation (recording start and end dates), ventilator-free days, days with delirium (indicating start and end dates), days of hospitalization with delirium, and days of sedation (with details of start and end dates). The duration of mechanical ventilation, the possible need for tracheostomy, the presence of adult respiratory distress syndrome, and the eventual occurrence of healthcare-associated pneumonia will also be documented.

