After the observation phase, essential data related to the patient's functionality and hospital stay will be collected. The Barthel Index at hospital discharge, cognitive function measured by the Montreal Cognitive Assessment (MOCA), and the quick sensitivity and dexterity test will be recorded, providing a detailed measure of the functional and cognitive capacity achieved. Additionally, the days of hospital stay and the length of stay in the Intensive Care Unit (ICU) will be documented, offering insights into the duration of the recovery process. Mortality will be evaluated, indicating whether it occurred during the observation period. Furthermore, functional independence will be measured using Activities of Daily Living (ADLs) at hospital discharge and ICU discharge, providing a comprehensive assessment of the impact of care and procedures on the patient's autonomy (see Annex 3 and 4).

Within the protocol, the inclusion of safety variables such as blood pressure alteration, cardiac arrhythmias, and oxygen desaturation highlights the importance of continuous monitoring of cardiovascular and respiratory health in patients. These variables serve as key markers to identify potential complications during the intervention or medical treatment. Early detection of blood pressure alterations provides crucial insights into perfusion and circulatory function. Monitoring cardiac arrhythmias aims to identify irregularities in heart rhythm while observing oxygen desaturation alerts to potential issues in tissue oxygenation. These safety measures, integrated into the protocol, contribute to a comprehensive evaluation and proactive management of any changes in the patient's condition, thereby supporting safety and well-being during the clinical process.

[figure not shown]

**Figure 1.** Study design diagram

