### Format of harvest of data

#### Data to the income:

##### Data of the Patient:

- Name of the Patient: \_\_\_\_\_
- Code: \_\_\_\_\_ (1,2,3...)
- Number of History Clinics: \_\_\_\_\_
- Sex \_\_\_\_\_
- Ethnicity \_\_\_\_\_ (Afro-Colombian, ROM, Indigenous, Raizal, None)
- Barthel index \_\_\_\_\_
- Mass Index Bodily \_\_\_\_\_
- Diagnostic \_\_\_\_\_ Code diagnosis CI10.
- Cluster to the that belong \_\_\_\_\_ (Early vs late)
- Boarding unit \_\_\_\_\_ (1 = surgical, 2 = neurological, 3 = Septic and Respiratory, 4 = Cardiovascular, 5 = Burns)
- SOFA Score \_\_\_\_\_
- APACHE II Score \_\_\_\_\_
- Punctuation SAPS II \_\_\_\_\_
- Date of Income: \_\_\_\_\_
- Date of Egress: \_\_\_\_\_
- Time from the Intubation until the Start of the therapy: \_\_\_\_\_

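### Annex 5 ties days of hospital stay to the day of ICU transfer, although the protocol lists hospital stay and ICU stay as separate outcomes

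*Protocol*

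**What the plan says.** **Outcome lists.** The PICOT table in Section 3 and the list in Section 6.6 both include "Days of hospital stay" and, as a separate item, length of stay in the ICU. The PICOT table places them under secondary outcomes, Section 6.6 under exploratory outcomes. Section 6.7 says that "the days of hospital stay and the length of stay in the Intensive Care Unit (ICU) will be documented".

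**Variable table (Section 6.11).** Hospital stay has its own row, but the definition only repeats the variable's name. No start or end event is given.

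**Data form (Annex 5, Functionality and Stay).** The hospital-stay item carries the note "the day when the intensivist informs transfer to the floor". The next item, "Time of Stay in ICU", gives only its unit, days.

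**ICU discharge (Section 6.5).** Discharge from the ICU is "defined as the moment when the intensivist determines that the patient can be transferred to hospitalization or discharged from the hospital".

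**Dates.** The admission part of the form collects "Date of Income" and "Date of Egress". Section 6.7 mentions "temporal data such as admission date, discharge date". Neither place says whether these are hospital or ICU dates.

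**The concern.** The note beside hospital stay names the event that ends the ICU stay. A patient who moves to a ward is still in hospital, so a count that stops at transfer does not measure hospital stay.

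Section 6.11 makes Annex 5 the instrument for data capture in REDCap, so this note is the only operational definition that staff will see. Section 2 presents ICU stay and hospital stay as distinct benefits of early rehabilitation. If the field follows the note, a difference between arms that arises on the ward would not show in it, and the reported hospital stay would be too short. Double data entry would not catch this, because both people would apply the same instruction.

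**Working it through.** The protocol states no figure here, so the check is of definitions. Let:

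- H0 = hospital admission
- I0 = ICU admission
- T = transfer from ICU to ward
- H1 = hospital discharge or death in hospital

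**Step 1: what each quantity measures, for a patient who goes to a ward.**

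- Hospital stay in the ordinary sense: H1 − H0
- ICU stay, using the Section 6.5 event: T − I0
- The Annex 5 hospital-stay item as annotated: T − H0 if counted from hospital admission, or T − I0 if counted from ICU admission (no start is given)

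**Step 2: what is left out.** Counted from hospital admission, the item falls short by (H1 − H0) − (T − H0) = H1 − T, which is all the ward days. Counted from ICU admission, it also omits I0 − H0, the days before the ICU.

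**Step 3: overlap with ICU stay.** Counted from ICU admission, the two items are identical. Counted from hospital admission, they differ only by I0 − H0. Section 6.1 allows intubation in the emergency or surgery rooms, so I0 − H0 need not be zero.

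**Step 4: who is affected.** Every patient transferred from the ICU to a ward, including any who later die there. Patients who die in the ICU, or who go home directly from it (a route that Section 6.5 allows), have no ward days to lose.

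**Step 5: can the form's two dates repair it?**

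| Admission date means | Egress date means | Hospital stay H1 − H0 recoverable? |
|---|---|---|
| Hospital | Hospital | Yes |
| ICU | Hospital | Ward days yes; days before the ICU no |
| Hospital | ICU | No: ward days missing |
| ICU | ICU | No: both parts missing |

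The documents do not settle which row applies. Section 6.7 places the two dates among the data collected on admission, and its first measurement moment is admission to the intensive care unit, which makes ICU dates possible. On the other side, the PICOT table plans measurements on the day of hospital discharge, and Annex 5 has Barthel and ADL items tied to hospital discharge, so staff are expected to follow the patient that far. The form elsewhere distinguishes hospital egress from ICU egress, so the unqualified egress date is ambiguous.

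**The case against.** The strongest reply is that this is a misplaced note in a roughly translated annex. It fits the ICU-stay item one line below, and the main text consistently keeps the two stays apart. The note also has no verb and no start event, so reading it as an instruction to stop counting is an inference. This may well describe how the note arose. It does not remove the problem, because the form is what staff complete and Section 6.11 offers no definition to override it.

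Three stronger readings are tempting and are not supported:

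- **That the hospital-stay outcome is lost.** A reader might infer this from the note alone. The form also collects two dates, and if both are hospital dates the stay can be derived whatever is entered in the annotated item. What can be said is that recovery is not assured.
- **That hospital stay simply becomes ICU stay.** This is exact only with a common start, and none is stated.
- **That the affected share follows from the 23% to 51% hospital mortality in Section 2.** Those figures are background for ventilated patients in general, whereas this trial excludes cardiac arrest and a life expectancy under 180 days and requires a Barthel index of at least 70. Nor is hospital survival the same as transfer to a ward: patients who die on the ward were transferred, and patients who go home from the ICU were not.

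It is also fair to say that the outcome is of limited rank. Even the higher placement, in the PICOT table, is only secondary.

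**Conclusion.** The contradiction stands. Annex 5 attaches the protocol's ICU-discharge event to hospital stay, which the protocol lists as an outcome distinct from ICU stay, and no other place supplies a correcting definition. If staff follow the note, the field omits the ward days of every patient transferred to a ward and largely duplicates ICU stay.

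This rests on two conditions: that the note is applied as printed, and that the analysis uses this field rather than dates. If both form dates are hospital dates and the stay is derived from them, the consequence disappears and only a mislabelled item remains. The protocol gives no ward-stay figure, so the bias cannot be put in days.

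The primary outcome, the safety outcomes and the sample size of 37 per group are untouched. The correction is worth making because it is cheap and concerns a listed outcome, but it does not threaten the trial's main conclusion.

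**What to change.** 1. In the Section 6.11 variable table and in Annex 5, define days of hospital stay as the time from hospital admission to hospital discharge.
2. Move the note about transfer to the floor from the hospital-stay item to the ICU-stay item.
3. Label both "Date of Income" and "Date of Egress" as hospital or ICU dates. If either is an ICU date, add the corresponding hospital date to the form.

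Relabelling alone is a small edit to the annex and to REDCap. If the existing dates are ICU dates, the cost rises to one or two extra date fields. For any patient already enrolled, the missing dates would have to be retrieved from the clinical record. No extra visit or measurement is needed, and no analysis of the primary outcome changes.

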### Variables of security:

- Outcomes:
  - The number of events adverse.
    - Altered blood pressure \_\_\_\_\_ (Yes/ No) (decrease of PAM > 15%)
    - Cardiac arrhythmia \_\_\_\_\_ (Yes/No)
    - Oxygen desaturation \_\_\_\_\_ (Yes/ No) (decrease minor at 80%)
    - Pain either agitation \_\_\_\_\_ (Yes/No)
    - Removal of line invasive \_\_\_\_\_ (Yes/No)

- Gastrointestinal (nausea, threw up either diarrhea) \_\_\_\_ (Yes/No)
- Tachypnea \_\_\_\_ (Yes/No)
- State neurological altered \_\_\_\_ (Yes/No)
- Number of events adverse serious \_\_\_\_
- Extubation not scheduled \_\_\_\_ (Yes/No)
- Pneumonia associated with careful health \_\_\_\_ (Yes/No)
- Bronchoaspiration \_\_\_\_ (Yes/No)

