### *Safety*

- Outcomes:

- Number of adverse events.
  - Altered blood pressure
  - Cardiac arrhythmia
  - Oxygen desaturation
  - Pain or agitation
  - Invasive line removal

- Gastrointestinal (nausea, vomiting or diarrhea)
- Tachypnea
- Altered neurological status
- Number of serious adverse events
- Unscheduled extubation
- Healthcare-associated pneumonia
- Bronchoaspiration

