| Dysphonia at 72 hours.       | Presence of dysphonia 72 hours after extubation.                                                                  | Qualitative Nominal | 0: No
1: Yes                                                                                                                                                                                                                                    |
| OMAHA+                | The use of the OMAHA+ Scale during the process of withdrawing ventilatory support to make the extubation decision | Qualitative Nominal | NOT = 0
Yes = 1                                                                                                                                                                                                                                 |
| Alteration in blood pressure | The patient experiences significant changes in blood pressure during the therapies                                | Nominal qualitative | 0 = No

1 = Hypotension without the requirement for medical management

2 = Hypotension requiring medical management

3 = Hypertension without requiring medical management

4 = Hypertension requiring medical management |
| Cardiac arrhythmias          | The patient had a cardiac arrhythmia during therapy.                                                              | Nominal qualitative | 0 = No

1 = Cardiac arrhythmia without a requirement for medical management

2 = Cardiac arrhythmia requiring medical management                                                                                                       |
| oxygen desaturation          | The patient became desaturated during therapy                                                                     | Nominal qualitative | 0 = No

1 = Oxygen desaturation without requirement for medical management                                                                                                                                                                   |

|                         |                                                                                 |                     |                                                                                                                                                    |

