### **Data collection instrument**

The clinical investigators will be responsible for collecting the information in RedCap (see Annex 5). RedCap provides a secure environment for the storage and management of clinical data, ensuring the privacy and confidentiality of the information. This transfer to RedCap will allow for better organization and access to the data, facilitating its analysis and subsequent use in the study.

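### The Annex 5 safety form contradicts the section 6.11 variable table and does not directly capture the section 6.6 outcome of the number of adverse events

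*Protocol*

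**What the plan says.** Protocol section 6.6 (Outcomes, Safety) lists "Number of adverse events" as an outcome, with eight types beneath it: blood pressure, arrhythmia, desaturation, pain or agitation, line removal, gastrointestinal, tachypnea and neurological status. The safety objective in section 5 compares the arms in terms of adverse events.

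The variable table in section 6.11 codes blood pressure 0 to 4, separating hypotension from hypertension and managed from unmanaged; one level is "3 = Hypertension without requiring medical management". Arrhythmia, desaturation, pain or agitation, tachypnea and neurological deterioration are coded 0/1/2 by need for medical management. Line removal is 0/1.

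The collection instrument is named in section 6.11: "The clinical investigators will be responsible for collecting the information in RedCap (see Annex 5"). In the safety block of Annex 5, the line "The number of events adverse" has no blank for a number. Each of the eight types below it is one Yes/No. Blood pressure reads "Yes/ No) (decrease of PAM > 15" per cent and desaturation reads "Yes/ No) (decrease minor at 80" per cent. The line "Number of events adverse serious" does have a numeric blank.

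**The concern.** The variable table says what will be analysed, and the form says what will be collected. Where the form holds less than the table, the difference is lost at the bedside, and no later analysis plan can recover it.

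The loss falls on the safety comparison. The arms differ by design in when therapy starts (under 24 hours against 72 hours), so the early arm may have more sessions in which an event can occur. Section 4 of the Protocol itself cites a 750-patient trial with more adverse events under early mobilization. An excess of managed events, of hypertension or of repeated events in the early arm is what the safety objective should be able to show.

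**Working it through.** The plan states no figure to reproduce here, so the check sets the two lists side by side.

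| Event type | Section 6.11 | Annex 5 | Lost or mismatched |
|---|---|---|---|
| Blood pressure | 0–4, four non-zero codes | Yes/No, fall in mean arterial pressure above 15% only | Severity; hypertension (codes 3 and 4) |
| Arrhythmia | 0/1/2 | Yes/No | Severity |
| Desaturation | 0/1/2, no saturation threshold | Yes/No, 80% cut-off | Severity; definition differs |
| Pain or agitation | 0/1/2 | Yes/No | Severity |
| Tachypnea | 0/1/2 | Yes/No | Severity |
| Neurological | 0/1/2 | Yes/No | Severity |
| Line removal | 0/1 | Yes/No | Nothing |
| Gastrointestinal | No entry | Yes/No | On the form and in 6.6, absent from 6.11 |

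Non-zero codes in section 6.11: 4 + 2 + 2 + 2 + 2 + 2 + 1 = 15 over seven types. Annex 5 has seven Yes boxes for the same types, plus one for gastrointestinal events. The managed/unmanaged split is lost for six types.

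**What count can be derived.** The safety block states no completion frequency.

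- One entry per stay: the only derivable number is how many types occurred, 0 to 8.
- One entry per day: the sum is event-days per type. Annex 1 schedules respiratory 3, physiotherapy 2, speech 2 and occupational 1–2 sessions, that is 8 to 9 a day, so two events of one type on one day still give one Yes.

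**Illustration of size, under assumptions.** Let p be the chance of one event type in one session, equal and independent across sessions. Take p = 0.8%, 2% and 5%, and 40 sessions per stay (5 days at 8 a day). These are assumptions. The lowest value borrows the share of activities discontinued in a study cited in section 4, which is not a rate for one event type.

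Expected events = 40p. Expected Yes with one entry per stay = 1 − (1 − p)^40.

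| p | Events | Yes per stay | Loss |
|---|---|---|---|
| 0.8% | 0.32 | 0.27 | 14% |
| 2% | 0.80 | 0.55 | 31% |
| 5% | 2.00 | 0.87 | 56% |

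If the early arm has two more days (56 sessions against 40), the true event ratio is 56/40 = 1.40. The ratio of Yes answers, [1 − (1 − p)^56] / [1 − (1 − p)^40], is 1.32, 1.22 and 1.08.

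With daily entry the loss is much smaller. Events per day are 8p and event-days are 1 − (1 − p)^8: 0.064 against 0.062, 0.160 against 0.149, and 0.400 against 0.337, losses of about 3%, 7% and 16%. With equal sessions per day, the 7-to-5-day ratio of 1.40 is preserved.

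**The case against.** The strongest reply is that Annex 5 never says the safety block is filled once per stay. Section 6.7 promises continuous measurement of safety outcomes, and section 6.11 (Procedures for Data Collection) says the therapists' variables are recorded daily. A reader might infer from the form that no count of adverse events could be computed at all. The documents do not support that: event-days could be summed under daily entry, and event types under single entry. Section 6.11 has no count field either, so the form's departure from the table is not what causes that gap. This stands. What remains is that the counting rule and frequency are not fixed, that the explicit every-day instruction in Annex 5 belongs to the observation block and not the safety block, and that daily entry restores neither severity nor hypertension.

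A reader might also infer that a saturation of 80–89% is a protocol-defined event that the form misses. It is not. Section 6.5 does name "a percutaneous oxygen saturation greater than or equal to 90" per cent, but as a condition for mobilization and not as an event definition, and section 6.11 gives no threshold. The Annex 5 wording is garbled in translation; below 80% is the likely reading, not a certain one. What can be said is that the form has a cut-off that the table lacks.

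It is also fair that only blood pressure and desaturation carry narrower definitions on the form, that serious events, unscheduled extubation, pneumonia and bronchoaspiration have their own fields, and that the built RedCap form is not shown.

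**Conclusion.** The contradiction is real and should be fixed. On the form as written, severity cannot be entered for six event types, hypertension cannot be entered at all, desaturation has a cut-off absent from the variable table, gastrointestinal events are missing from that table, and the number of adverse events is not directly captured. These points follow from the text and need no assumption, except that data are entered on Annex 5 as printed.

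How much of the count is lost depends on entry frequency, which the safety block leaves open. The 14% to 56% loss and the shrinkage of a ratio of 1.40 to between 1.32 and 1.08 apply only to once-per-stay entry with assumed session numbers and probabilities; they are not estimates for this trial. The primary outcome, its analysis and the sample size are untouched.

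**What to change.** Before further enrolment, revise the Annex 5 and RedCap safety block so that each event is recorded with its date and its section 6.11 code, for example one line per event. Derive the number of adverse events from these records and state that rule in the Protocol. Add the gastrointestinal item to section 6.11. Reconcile the blood-pressure and desaturation definitions so that one definition of each appears in both section 6.11 and Annex 5; which clinical threshold applies is for the sponsor to decide.

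The cost is one form revision and slightly more entry time per event. Therapists already record their variables daily, so the added burden should be small.
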